# Anticoagulated patient’s perception of their illness, their beliefs about the anticoagulant therapy prescribed and the relationship with adherence: impact of novel oral anticoagulant therapy – study protocol for The Switching Study: a prospective cohort study

**DOI:** 10.1186/s12878-016-0061-9

**Published:** 2016-08-23

**Keywords:** Anticoagulants, Atrial fibrillation, Beliefs, Illness perceptions, Medication adherence, Venous thromboembolism, Quality of life

## Abstract

**Background:**

Anticoagulant therapy is prescribed for millions of patients worldwide for the prevention and treatment of both arterial and venous thrombosis. Historically, only vitamin K antagonists have been available for clinicians to prescribe. The anticoagulation landscape is changing. The recent availability of the novel oral anticoagulants overcome many of the disadvantages associated with vitamin K antagonists. However the lack of formal monitoring and clinic follow-up is a concern for clinicians, as medication adherence is being assumed, which is known to decline in patients prescribed medications for chronic conditions. The switching study is a programme of work investigating the association between medication adherence and patient’s beliefs about anticoagulation therapy (warfarin and subsequently novel oral anticoagulants), together with beliefs about their illness and anticoagulation related quality of life.

**Methods/design:**

The anticoagulation database at King’s College Hospital will be interrogated and two groups of patients will be identified; those with a time in therapeutic range on warfarin of ≥75 % and those <50 %. These groups of patients will have their illness perceptions, anticoagulation specific quality of life and beliefs about medications compared. Those patients in the time in therapeutic range <50 % group, will be then be invited to switch to a novel oral anticoagulant, as per local guidance. Those patients, who do switch, will then be followed longitudinally and have their adherence, illness perceptions, anticoagulation specific quality of life and beliefs about medications, re-evaluated on the novel agent. The results from these sub-studies, will inform a clinical pathway to support patients on these novel agents, which will be evaluated in an independent group of patients.

**Discussion:**

The results from the switching study will be used to develop a clinical pathway to support patient’s prescribed novel oral anticoagulant therapy long-term.

**Electronic supplementary material:**

The online version of this article (doi:10.1186/s12878-016-0061-9) contains supplementary material, which is available to authorized users.

## Background

Anticoagulant therapy is prescribed for millions of patient’s world-wide, most commonly for the acute treatment and long-term prevention of venous thromboembolism (VTE) and as primary and secondary prevention of stroke in the context of atrial fibrillation (AF) [1, 2]. Until recently the majority of patients requiring chronic anticoagulant therapy were prescribed vitamin K antagonists (VKA), as these were the only oral anticoagulant agents available [1, 2]. VKA therapy comes with some practical disadvantages; need for monitoring and a relatively significant number of drug-drug and drug-food interactions, which has meant that not all patients eligible have benefitted from these agents in the past [3]. In recent years, the aforementioned disadvantages has led to the development of new classes of oral anticoagulants, the direct thrombin inhibitor (dabigatran) and the direct Xa inhibitors (apixaban, betrixaban, edoxaban, rivaroxaban). These agents hold many advantages over VKA, primarily of a predictable pharmacokinetic nature, meaning that there is minimal requirement for regular monitoring of anticoagulant effect [4]. In the United Kingdom (UK), the available direct oral anticoagulants, apixaban, dabigatran, edoxaban and rivaroxaban are all approved for AF and VTE indications and available for clinicians to prescribe as treatment options, when clinically indicated [5–13]. Indeed their availability has sparked local initiatives to ensure that patients in AF with a CHA_2_DS_2_VASc score [14] of two or above are offered oral anticoagulation, be it with VKA or the novel agents, referred to herein as NOAC. The general perception is, that the NOACs are *easier* to use, so uptake both from a clinician (prescribing) and patient (receiving) perspective is likely to be higher, with cost analyses modelling suggesting that these agents are cost-effective [5–13]. Treatment pathways across the UK are being revisited to accommodate these agents and the advantages they bring. However, these agents are not free from risks. Compared to VKA, little experience exists on how these agents perform long-term, e.g. in minimising complications associated with VTE such as the post-thrombotic syndrome. Additionally, there are currently no antidotes available for the direct Xa inhibitors; a situation which is likely to change in the coming months. Finally, the benefits cited for the NOACs assume that patients actually take the medication as prescribed. Research suggests that approximately 30–50 % of medication prescribed for chronic conditions are not taken as intended [15]; adherence is often found to be high during the initial months of therapy and then found to decline in many patients [16], with clinician’s ability to recognise medication non-adherence reported to be poor [17–20]. Medication non-adherence not only impacts negatively on the patient concerned, the wider health-care economy is adversely affected [21]. Research confirms that individual patient’s beliefs about medicines are a strong predictor of their adherence to treatment. These beliefs can be grouped under two categories; (1) perceptions of necessity and (2) concerns about negative effects [22]. Therefore beliefs that failure to take the treatment could result in adverse consequences is associated with higher adherence rates (and vice versa). Acknowledging that all patients will have differing beliefs about their medications is the first step in addressing the medication non-adherence problem [22, 23].

With the availability of NOAC therapy, an opportunity now exists to re-visit patients who are currently prescribed VKA with poor anticoagulation control, and consider switching their anticoagulant therapy to a NOAC. The question is how to determine *success* or *failure* on VKA. A common method of determining good anticoagulation control on VKA is through their time in therapeutic range (TTR). The Rosendaal method [24] is the most widely used method to calculate TTR and uses linear interpolation to calculate an INR value for each day between observed INR values (over a 1 year period). The TTR represents the percentage of these INR values in days that are in the therapeutic range. The TTR is a valid marker to use in clinic, as it has been reported to predict clinical outcomes such as major bleeding, stroke and systemic embolic events [25]. TTR provides a means, however imperfect [26], of identifying possible medication non-adherence and/or whether the patient may benefit from a switch to NOAC. In the UK, national guidelines suggest using the TTR criteria for determining which patients might be prioritised for switching to a NOAC. Indeed, the recently published National Institute for Care Excellence guidelines for AF stipulate that anticoagulation clinics should reassess anticoagulation for patients with poor anticoagulation control, and one of the criterion specified for re-assessment is if a patient’s TTR is <65 % [27].

Non-adherence in the context of anticoagulant therapy is not new and the issue has received attention from researchers in the past [28–32], with the importance of non-adherence to NOAC now emerging [33–35]. Little research exists on what patients general and specific concerns or necessity might be about the VKA that they are currently prescribed. This is important, as with a significant change in the anticoagulation landscape, understanding the patient perspective, particularly those with poor TTR, could help identify patterns of concerns that this group of patients may have, which could impact on their medication taking behaviour, if switched to a NOAC. Studying this would help with service delivery and determine if a specific clinical pathway would support adherence with chronic anticoagulant therapy in those identified or suspected of poor adherence - as currently, no long term pathway for NOAC patients is expected to be in place.

The Switching study is a series of prospective studies designed to investigate the association between medication adherence and patients’ beliefs about anticoagulation therapy (warfarin and subsequently NOAC) together with beliefs about their illness and anticoagulation-related quality of life.

The Switching study aims to test the following hypotheses:*Patients’ beliefs about warfarin and their illness perceptions is associated with their adherence to warfarin as measured by time in treatment range (TTR), over and above any clinical or demographic variables.**Patients’ beliefs about NOAC at baseline and their illness perception can predict their adherence to NOAC, over and above any clinical or demographic variables.**Patients with symptomatic disease (either VTE or AF) have higher necessity scores for anticoagulant treatment compared to patients with asymptomatic disease.**Patients with a TTR >75 % have low concerns and higher necessity scores for warfarin than those with a TTR <50 %.**Patient’s responses to the illness perception questionnaire (IPQ) is specific to treatment and will change, following a switch to NOAC.**Patient’s quality of life scores improve following a switch to NOAC.*

## Methods/design

### Patients and patient selection

Anticoagulated patients who meet the inclusion criteria, defined by their TTR, will be identified through the DAWN® databases used at King’s College Hospital NHS Foundation Trust. King’s College Hospital is a large teaching hospital, based in South East London, providing specialist tertiary services of liver disease and transplantation, neurosciences, haemato-oncology, cardiology and foetal medicine. The anticoagulation service at King’s is provided between two hospital sites; Denmark Hill and Bromley. The combined anticoagulation population is ~6, 000 patients, with a clinic average TTR of 76 and 73 % for the Denmark Hill and Bromley sites respectively.

Patient selection for the studies will be dictated by their current time TTR, as per protocol and whether patients fit the eligibility criteria. The anticoagulant clinic at King’s utilises the DAWN® software, and the TTR is calculated for patient’s prescribed chronic anticoagulation, by reviewing INR values 1 year from the date of calculation. The TTR calculation utilises the Rosendaal method [24].

### Psychometric instruments

The instruments which will be administered to patients in this study comprise of the Beliefs about Medicines Questionnaire (BMQ) [36], the revised Illness Perception Questionnaire (IPQ-R) [37] and the Anti-Clot Treatment Scale (ACTS) [38] quality of life instrument. The BMQ is a validated instrument for assessing patient’s beliefs about medicines in general (overuse and harm) and their prescribed medication specifically (necessity and concerns). The IPQ-R is a validated instrument that assesses patient’s perception of their illness. The measures *identity -* the symptoms the patient associates with the illness, *cause* - personal ideas about aetiology, *time-line* - the perceived duration of the illness (chronicity) and how it fluctuates (cyclical), *consequences* - expected effects and outcome and *cure control* - how one controls or recovers from the illness (personal control) and the treatments available to manage it (treatment control). There is also a global measure of *illness coherence* – the degree to which the illness makes sense to the patient and *emotional representation* - a measure of the impact of the illness on their emotional well-being. The ACTS is a 17-item anticoagulation specific quality of life instrument which measures burden (a 12-item scale) and benefits (a 3 -item scale). The questionnaire packs administered to patients in the Switching study are available as Additional files 1, 2, 3 and 4 with this manuscript.

### Switching study series

#### Study I

For study I, two groups of patients prescribed chronic VKA for the primary and secondary prevention of stroke in the context of AF and for treatment and secondary prevention of VTE, will be recruited: those with a TTR >75 % (group 1) and those with a TTR <50 % (group 2). The TTR cut-off’s of >75 and <50 % were chosen to inform groups 1 and 2, based on the availability of the NOACs providing an opportunity to switch patients poorly controlled on VKA; it was felt that the patients with the poorest control should be given this option to switch first, i.e. be prioritised. Furthermore, having two distinct groups (<50 and >75 %) and understanding and appreciating the differences between these two groups will ensure that the hypotheses posed could be tested and if appropriate, a suitable support mechanism can be developed for patients prescribed chronic NOAC therapy where it is anticipated that adherence might be an issue.

For group 1 patients, their illness perception for why they are prescribed anticoagulant therapy, their beliefs about VKA and their anticoagulation specific quality of life explored through the aforementioned psychometric instruments [36–38], once through the post. Eligible patients will be consecutively identified from the DAWN® database. These patients will remain on VKA therapy, due to their excellent TTR.

In contrast, group 2 patients, due to their poor TTR will specifically be invited to clinic (visit 1) to have their beliefs about warfarin, their perception of their illness and their quality of life explored through the aforementioned validated instruments. Study I will assess the association between adherence to warfarin and i) patient beliefs about treatment and ii) patient perception of their illness and compare responses from group 1 and group 2 patients. In addition, a baseline level for patient’s anticoagulation-specific quality of life will be established.

#### Study II

Following completion of the psychometric instruments, patients in group 2 (from study I) will be asked if they wish to switch to a NOAC, according to local guidelines. Patients who then switch will prospectively be followed in clinic will be required to return for a clinic visit at 1, 2 months and 1 year into NOAC treatment allowing for the longitudinal assessment of adherence. At their 1-month follow-up visit (visit 2), patients will be given a questionnaire pack comprising of validated instruments designed to assess their newly established beliefs about NOAC therapy and any short-term changes in quality of life. The same instruments will be administered at their 1-year follow-up (visit 4) to determine whether any changes in beliefs, illness perceptions and quality of life are sustained. The questionnaire pack will be posted to the patient, prior to their clinic visit 4, requesting them to complete and bring along to their clinic appointment. To prevent participant burden, no questionnaires will be administered at the 2-month follow-up visit (visit 3). However, at 1-month and 2-month follow-up visits (visits 2 and 3), patients will be asked to bring in their NOAC medication to clinic, so a pill count can be conducted by the reviewing clinician.

Patients identified in this group who decline a switch to a novel agent, will also be followed longitudinally for the duration of the study and any clinically relevant outcomes will be reported. Furthermore, their reasons for not wishing to switch, will formally be recorded and described.

Analysis for studies I and II will be conducted on an intention to treat basis.

#### Study III

Following completion of studies I and II, the data collected will be analysed and used to design a clinical pathway which will be evaluated in a third (independent) group of patients (group 3 – patients with a TTR <50 %). The clinical pathway will be informed from the 2-month follow-up data collected up to visit 3 from patients in group 2 of study II. Group 3 patients will have the same follow-up in clinic as per the schedule outlined for group 2 patients, and analysis for study III will also be conducted on an intention to treat basis. The findings from group 2 patients (beliefs about medicines, illness perceptions, quality of life and adherence to anticoagulant therapy) will then be compared to the findings from group 3 patients. In this way, this controlled study design will then allow an assessment of the effectiveness of the clinical pathway developed. Figure 1 summarises the three studies which form this programme of work.

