### Study outcomes

Individual % medication adherence to direct acting anticoagulant therapy (1 year following switch)Changes in patients beliefs about the anticoagulation therapy prescribed, at 1 month and 1 year following a switch to NOAC therapyChanges in patients illness perceptions (1 month and 1 year following switch)Changes in patients anticoagulation specific quality of life (1 month and 1 year following switch)Persistence with NOAC therapy, following a switch from VKA (1 year following switch)

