### Sample size and statistical analysis

#### Study I & II

Patients who are >75 % in TTR (group 1) will be classified as adherent and those who are <50 % in TTR (group 2) will be classified as non-adherent. To determine if patients’ beliefs about warfarin and their illness perception is associated with their adherence status, univariate analyses will first be conducted to identify the key variables that will be entered into the multiple logistic regression model. Assuming a recruitment ratio of 1:1 of non-adherent : adherent patients, a total sample size of 180 to 240 patients will be able to accommodate 6 to 8 predictive variables. i.e. up to 120 patients who are adherent and up to 120 patients who are non-adherent are required as measured by TTR.

Multiple linear regression will be used to examine whether illness and treatment beliefs can predict adherence to NOAC. Using the formula that 15 observations are needed per degree of freedom, a sample size of 240 will be able to test whether illness and treatment beliefs (11 dimensions) and up to five demographic/clinical variables can predict adherence to NOAC. Therefore a sample size of 240 patients who are switched to NOAC is required.

However, as the refusal rate for switching to NOAC for eligible patients is not known, and given that the NOAC patient sample will derive from those who are non-adherent to warfarin (<50 % TTR), at least 240 patients – rather than 120 patients - who are non-adherent will need to be recruited in order to be able to perform both the linear regression analysis and logistic regression analysis. A conservative refusal rate of 30 % would suggest 342 patients who are <50 % TTR on warfarin would need to be recruited into group 2.

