#### Study III

Three hundred forty-two patients will be recruited into group 2 which will act as the control group. Power calculations (GPower 3.1) assuming one-tailed analysis using an independent groups design, suggest that a 1:1 matching i.e. recruiting 342 patients into the intervention group (group 3) would allow for the detection of a small-sized effect of the intervention (d = 0.20).

The Switching study has been reviewed and given a favorable opinion by the London-Dulwich Research Ethics Committee: REC reference: 13/LO/1468.

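### Study III names no deciding outcome for the pathway's effectiveness, and its d = 0.20 power statement is tied to no outcome

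*Protocol article*

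**What the plan says.** In the protocol article, the Study III section under Switching study series sets group 3, which receives the pathway, against group 2, which does not: "The findings from group 2 patients (beliefs about medicines, illness perceptions, quality of life and adherence to anticoagulant therapy) will then be compared" with those of group 3. It concludes that "this controlled study design will then allow an assessment of the effectiveness of the clinical pathway developed".

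The Study outcomes section lists five outcomes for the whole programme. The first is "Individual % medication adherence to direct acting anticoagulant therapy (1 year following switch". Beliefs, illness perceptions and quality of life follow, each at 1 month and 1 year, and then persistence at 1 year. None is called primary and none is assigned to Study III. None of the six hypotheses at the end of the Background concerns the pathway.

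The Study III sample size paragraph states that "Three hundred forty-two patients will be recruited into group 2 which will act as the control group". The calculation is described as "assuming one-tailed analysis using an independent groups design", and a further 342 in group 3 "would allow for the detection of a small-sized effect of the intervention (d = 0.20". Alpha, power and the outcome are not given.

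**The concern.** The article draws a conclusion about effectiveness from four domains, most of them made up of several scales, without saying which result decides. Adherence could be the same in both groups while one belief or illness-perception scale differs by chance, and nothing in the text would prevent that difference from being reported as a benefit of the pathway.

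The power statement has the same gap. A standardised difference of 0.20 means something only for a named variable, measured in a known set of patients. One of the four domains, NOAC adherence, exists only in patients who switch, and the programme itself expects some to decline. A one-tailed test also needs a direction of benefit, whereas the outcome list describes beliefs and illness perceptions only as changes.

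**Working it through.** **1. The plan's own figure.** Inputs from the Study III sample size paragraph: n = 342 per group, d = 0.20, one-tailed, two independent groups. Alpha is not stated; 5% is assumed.

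Power = Φ(d·√(n/2) − 1.645) = Φ(0.20 × √171 − 1.645) = Φ(2.615 − 1.645) = Φ(0.970) = 83% (the noncentral t also gives 83%).

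Detectable d at 80% power = (1.645 + 0.842) × √(2/342) = 0.19.

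So d = 0.20 agrees with the stated design for one test at one-sided 5%. At one-sided 2.5% the power would be 74%.

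**2. False-positive chance if any one result could decide.** Assumptions: each test is one-sided at 5%, unadjusted, with a defined direction of benefit, and any nominally significant result counts.

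For k independent tests the chance is 1 − 0.95^k. For tests with common correlation ρ it is 1 − ∫ Φ((1.645 − √ρ·z)/√(1−ρ))^k φ(z) dz.

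Two counts are used:
- k = 4, one test for each domain named in the Study III section.
- k = 14, one test per scale at one time point. This is 11 for "illness and treatment beliefs (11 dimensions" (the count in the Study I & II sample size section, where they serve as regression predictors), 2 for the quality-of-life instrument, which "measures burden (a 12-item scale) and benefits (a 3 -item scale", and 1 for adherence.

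| Tests | ρ = 0 | ρ = 0.3 | ρ = 0.5 |
|---|---|---|---|
| 4 | 18.5% | 16.4% | 14.4% |
| 14 | 51.2% | 37.2% | 29.1% |

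**3. Price of keeping every outcome as deciding.** With Bonferroni at 5%/k, 342 per group and d = 0.20, power per outcome is 64% for k = 4 and 47% for k = 14. Reaching 80% would need 476 or 624 per group.

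**4. Power if NOAC adherence decides.** The Study I & II sample size section reaches 342 from 240 switchers and a 30% refusal rate: 342 × 0.70 = 239.4, about 240. Assuming the same refusal in group 3:

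- Power at d = 0.20 = Φ(0.20 × √120 − 1.645) = Φ(2.191 − 1.645) = Φ(0.546) = 71%.
- Detectable d at 80% power = 2.487 × √(2/240) = 0.23.

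**5. Is 1-year adherence one measure?** No. Table 1 gives three sources at visit 4: the GP care record, self-report and the 8-item adherence scale. The Adherence to NOAC section adds missed doses over the last week and coverage from prescription records, the latter for persistence. Pill counts are made only at 1 and 2 months. The article does not say which source yields the individual percentage.

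**The case against.** A reader might infer that an ineffective pathway has a fixed chance of about 30-40% of appearing beneficial. The article does not support that. It says only that findings are compared and that the design permits an assessment; it states no rule that one significant scale suffices. The count of 14 borrows 11 dimensions that the article uses as predictors of adherence, not as Study III endpoints. A scale with no beneficial direction cannot produce a false benefit on a one-tailed test, and the article gives directions for only some: necessity and concerns in the fourth hypothesis, quality of life in the sixth. With the four domains actually named, the figure is at most 19%. All this stands, so the percentages are conditional illustrations.

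A reader might also infer that the deciding outcome could be chosen once all control results are known, because the pathway is to be designed after Studies I and II are complete. The same section goes on to say that the pathway draws on group 2 data up to visit 3, that is, 2 months. The 1-year control results are not what it is built on, so that inference goes too far.

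Finally, an alpha split, a testing order or a multiplicity method may sit in an analysis plan or full protocol that is not shown, and their absence here is not an error. What remains is narrower. The article itself states the effectiveness aim, the outcome list and the power figure, and never connects them. Naming the outcome that decides, and the one that was powered, belongs in the protocol.

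**Conclusion.** The point holds in limited form. Study III has no named deciding outcome, and its only power statement cannot be attached to any outcome. The d = 0.20 figure is reproducible for a single one-sided 5% test on all 342 per group (83% power), but alpha and target power have to be assumed.

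If any nominal success counted, the error rate would be about three to four times 5% with four tests (14-19%) and about six to ten times with 14 scales (29-51%). This rests on an assumed decision rule, alpha, test count and correlation.

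If adherence is the intended outcome, the relevant figure is nearer 71% power at d = 0.20, or 80% at d of about 0.23, given 30% refusal in both groups. The weakness lies in how the conclusion will be drawn; it does not show that a false conclusion is likely. It should be corrected.

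**What to change.** Before group 2's 1-year data are analysed, amend the Study III section, the Study outcomes list and the Study III sample size paragraph as follows.

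- Name one deciding contrast between groups 3 and 2. Individual percentage adherence to NOAC at 1 year is an obvious candidate because it is listed first.
- State which adherence source in Table 1 and the Adherence to NOAC section supplies that value, and how the percentage is derived.
- Label the remaining outcomes and time points secondary or exploratory, with no effectiveness claim resting on them alone.
- Tie the power statement to the named outcome, give alpha and power, and base it on the patients who can contribute. For 1-year adherence under 30% refusal, that is about 240 per group: 71% power at d = 0.20, or 80% at about 0.23.

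With one deciding test the error stays at its nominal 5%. The cost is mainly wording, with two real consequences: a benefit seen only on a secondary scale could not be claimed as pathway effectiveness, and the stated detectable effect becomes slightly less favourable.

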### Consent, confidentiality and data storage

Group 1 patients will be sent the study patient information leaflet, along with the study questionnaire and a pre-paid envelope, to return the completed questionnaire to the research team.

When group 2 patients are invited for the consultation in the anticoagulation clinic, they will be sent the study patient information and asked to read it prior to their clinic visit. At the clinic visit, the pharmacist in clinic will ask the patient if they wish to participate in the study and address any questions they may have. For those patients who indicate that they interested, the pharmacist will recruit them into the study. Informed written consent will be taken by the pharmacist. For those patients who do not wish to participate, the pharmacist will still offer the patient the opportunity to switch to a NOAC, as per local guidance.

A similar process to that of group 2 patients will be followed for group 3 patients, at the appropriate time for study III.

All recruited patients will be reviewed in Haematology outpatients at the respective hospitals, by pharmacists trained in the study.

Data collected for the purposes of the study will be recorded by the pharmacist on a pre-determined study form, which captures the information required for the study. At the earliest opportunity, the principal researcher associated with the study will transfer the data to an excel database at the respective hospitals and subsequently transfer to an SPSS database, with the hard copy of the data collection form being filed and stored in a locked office within the haematology department at King’s College Hospital, with only members of the clinical team having access to this office.

One week after entry of a patient’s data onto the SPSS database, the data which had been entered will be re-checked for any entry discrepancies by the principal researcher.

As soon as a patient consents to participate in the study, they will be given a unique study number. This number will be entered onto the SPSS database and will only be traceable back to an individual patient by accessing the study form for the patient in the haematology department at King’s College Hospital.

All electronic data will be encrypted and password protected.

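### Study III compares a later cohort with an earlier, non-randomised one, so a pathway effect cannot be told apart from calendar-time or case-mix differences, and the effectiveness claim goes beyond the design

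*Protocol article*

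**What the plan says.** The protocol article's section on Study III sets the order of events: "Following completion of studies I and II, the data collected will be analysed and used to design a clinical pathway". It names the source of the pathway: "The clinical pathway will be informed from the 2-month follow-up data collected up to visit 3 from patients in group 2 of study II". The pathway is then "evaluated in a third (independent) group of patients (group 3 – patients with a TTR <50" per cent). Group 3 has the same clinic follow-up as group 2, analysis is by intention to treat, and beliefs, illness perceptions, quality of life and adherence are compared between the two groups. From this the article concludes that "this controlled study design will then allow an assessment of the effectiveness of the clinical pathway developed".

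The sample-size section for Study III fixes the comparator: "Three hundred forty-two patients will be recruited into group 2 which will act as the control group". It describes the power calculation as "assuming one-tailed analysis using an independent groups design, suggest that a 1:1 matching", which it explains as recruiting 342 patients into group 3, and gives the detectable effect as d = 0.20. Alpha and power are not stated. No allocation step, matching variable or covariate is named.

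**The concern.** Group 2 is a historical control. Every group 2 patient belongs to the earlier period without the pathway and every group 3 patient to the later period with it. Whatever else differs between the periods enters the same contrast as the pathway.

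The article itself gives reasons to expect change. Its Background says that UK treatment pathways are being revised, that the lack of antidotes for the direct Xa inhibitors is likely to change within months, and that national guidance now prompts reassessment when TTR is below 65%. The one-year adherence and persistence outcomes are measured after prescribing has passed to the GP, so they are also exposed to changes in GP practice.

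At stake is what Study III may conclude. Its result is meant to support a long-term service for NOAC patients. If a difference between periods is read as an effect of the pathway, that service rests on evidence the design cannot supply.

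**Working it through.** **Inputs from the protocol article.** 342 per group, equal numbers, one-tailed independent-groups comparison, d = 0.20 (Study III sample size). 240 switchers required and a 30% refusal rate (Study I & II sample size).

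**Inputs assumed.** Alpha 5%, because the article states none. A favourable cohort shift b of 0.05 to 0.20 SD that has nothing to do with the pathway. The per-group number runs from 240 (only switchers contribute NOAC adherence data) to 342 (everyone contributes).

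**1. The article's own figures.** 240 / 0.70 = 342.9, against 342 stated, which agrees apart from rounding. The standard error of a standardised difference is sqrt(2/n) = sqrt(2/342) = 0.0765. Power is Phi(0.20/0.0765 − 1.645) = Phi(0.970) = 83.4% one-sided; 80% would need 310 per group. So 342 per group does detect d = 0.20, and the arithmetic is sound.

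Two-sided, power is Phi(0.20/0.0765 − 1.960) = Phi(0.655) = 74.4%; 80% would need 393 per group. With 240 per group, sqrt(2/240) = 0.0913, and power is 70.7% one-sided and 59.1% two-sided.

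**2. No pathway effect, but a cohort shift b.** The chance of a significant favourable result is Phi(b/sqrt(2/n) − 1.645), one-sided 5%:

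| Shift b (SD) | 240 per group | 342 per group |
|---|---|---|
| 0 | 5.0% | 5.0% |
| 0.05 | 13.6% | 16.1% |
| 0.10 | 29.1% | 36.8% |
| 0.15 | 49.9% | 62.4% |
| 0.20 | 70.7% | 83.4% |

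The last row equals the power in step 1. A drift as large as the target effect is exactly as likely to give a positive result as a real effect would be.

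**3. The same with a two-sided 5% test.** At b = 0.10: Phi(1.095 − 1.960) = 19% with 240 per group and Phi(1.308 − 1.960) = 26% with 342. At b = 0.20: 59% and 74%.

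**4. Drift in the other direction.** At b = −0.10 the one-sided test rejects in Phi(−1.095 − 1.645) = 0.3% (240) and Phi(−1.308 − 1.645) = 0.2% (342). An unfavourable drift would instead hide a real benefit.

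**The case against.** The case for the plan has substance.

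- **The title calls this a cohort study and no randomisation is claimed.** A historically controlled study is still a controlled one. This stands as far as the label goes. It does not support the step from the label to an assessment of effectiveness.
- **The cohorts are alike by design.** They share the TTR criterion, exclusions, service, visit schedule and baseline data. This limits case-mix differences. It does nothing about time trends.
- **Covariates may be in the full protocol or analysis plan.** A reader might infer that the comparison is unadjusted. The article does not say so: the independent-groups test appears in a power calculation, and silence on covariates in a condensed article is not a fault. The point survives, because no covariate set can separate cohort from calendar period when the two coincide.
- **Depletion of the low-TTR pool.** A reader might infer that group 3 must contain more newly low-TTR patients. Both cohorts "will be identified through the DAWN® databases used" at one service, the poorest-controlled patients are prioritised for switching, and for those who decline the study "the pharmacist will still offer the patient the opportunity to switch to a NOAC, as per local guidance". The two groups need 342 + 342 = 684 patients from about 6,000, or 11.4%. Depletion is therefore plausible, but not shown. The article does not give the number with TTR below 50%, does not say that all are invited before group 3 opens, and shows only that non-participants are offered a switch, not that they accept it.
- **One-tailed testing.** A reader might blame the bias on it. Step 3 shows that a two-sided test is also misled by drift, though less often. Sidedness affects the rate; it is not the source.
- **Direction.** The size and sign of any drift are unknown. It is too strong to say that drift will be credited to the pathway; the accurate statement is that the two cannot be told apart.

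**Conclusion.** The point holds as a limit on interpretation. Group 3 is compared with an earlier, non-randomised group 2 that also supplied the data for the pathway, and the stated conclusion about effectiveness claims more than this design can deliver. No error in the sample-size arithmetic was found.

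The size depends on assumptions. For a favourable shift of 0.1 SD with no pathway effect, a significant result is expected in 29% to 37% of studies at one-sided 5%, or 19% to 26% two-sided. The shift and the alpha are both assumed, and each range runs from 240 to 342 per group. The figures show how sensitive a study sized for d = 0.20 is; they do not predict that such a drift will occur.

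**What to change.** 1. Describe Study III as a before-after comparison with a historical control, and limit its conclusion to association.
2. Estimate the group 3 minus group 2 difference by regression adjusted for baseline variables already available: baseline TTR, age, gender, ethnicity, AF or VTE indication, symptomatic status, MRCI and the Charlson index. Where the outcome is an IPQ, BMQ or ACTS scale, add its visit 1 score. There is no visit 1 counterpart for NOAC adherence, and the visit 1 BMQ refers to warfarin, so there it serves only as a prognostic covariate. SAMe-TT2R2 need not be added, since it already contains sex, age and race.
3. Report two-sided 95% confidence intervals, and state alpha and power.
4. Examine outcome trends by enrolment date within group 2, as a check on drift before group 3 opens.
5. Replace the term 1:1 matching with 1:1 ratio, since only equal numbers are meant.
6. State that adjustment reduces measured case-mix differences but cannot remove confounding with calendar time.

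This needs new wording and some extra analysis, with no new data collection. The cost is a more modest claim and, at 342 per group, two-sided power for d = 0.20 of about 74% rather than 83% one-sided.
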